### 12.1.2 Discontinuation Procedures

If a subject discontinues the study because of safety concerns such as adverse events, the investigator or subinvestigator will take appropriate action for the subject. In addition, the investigator or subinvestigator will confirm safety in each discontinued subject and conduct examinations promptly upon discontinuation.

Any subject who does not return to the investigative site after receiving study treatment will be followed up to the extent possible, in a way that protects the subject’s human rights, and the predetermined assessment will be made.

The investigator or subinvestigator identifies the date of discontinuation and the reason for the discontinuation and records the information in the electronic case report form.

## 12.2 Discontinuation or Suspension at the Investigative Site

When the clinical study at the investigative site is discontinued or suspended for reasons such as there is a suspicion of safety regarding the investigational product, the investigator will promptly report it to the director of the investigative site in writing, and provide a detailed written explanation concerning study discontinuation or suspension. The director of the investigative site will immediately report study discontinuation or suspension and the reason in writing to the Sponsor and IRB.

The clinical study at the concerned investigative site will be discontinued in the following cases, and appropriate measures will be taken as described above.

1) When protocol amendment is instructed by the director of the investigative site based on the opinions of the IRB consulted by the director of the investigative site, but the Sponsor does not approve it.

2) When the IRB that is consulted by the director of the investigative site judges that the study should not be continued, and the director of the investigative site instructs study discontinuation.

3) When a serious or continuous violation of the GCP, this protocol, or the study contract occurs at the investigative site.

## 12.3 Discontinuation or Suspension of the Entire Study

When discontinuing or suspending the entire study in the course of a clinical study, the Sponsor will promptly notify all directors of the investigative sites and regulatory authority together with the detailed reason. When the director of the investigative site receives such a notice, he/she will promptly inform the investigator and IRB in writing together with the reason. When the study is discontinued or suspended, the investigator will promptly inform the subjects, and take necessary action such as supplying appropriate medical care.

# 13 Endpoints

## 13.1 Efficacy

### 13.1.1 Primary endpoint

• Intact PTH level change rate at the end of investigational product administration

### 13.1.2 Secondary endpoints

• Number and percentage of subjects achieving a decrease in intact PTH level of ≥30% (rate of change ≤-30%) at the end of investigational product administration

• Number and percentage of subjects achieving an intact PTH level of ≤240 pg/mL at the end of investigational product administration.

• At the time of each test and at the end of administration of the investigational product, Intact PTH level, whole PTH level, corrected serum Ca level, ionized Ca level, serum P level, intact FGF23 level, and corrected serum Ca-P product

### 13.1.3 Exploratory endpoints

• Bone metabolic markers at the end of investigational product administration and at the end of follow-up

• Parathyroid gland (volume and blood flow) at the end of investigational product administration

## 13.2 Safety endpoints

• Adverse events

• Lowest corrected serum Ca level from the start of investigational product administration until the end of follow-up

• Laboratory values

• Vital signs

• 12-Lead electrocardiography

• Ophthalmologic examination

## 13.3 Pharmacokinetic endpoint

• Plasma KHK7580 level

# 14 Statistical Analysis

## 14.1 Statistical Methods

The major efficacy and safety endpoints and their analytical methods are as follows. As a general rule, categorical data are summarized using frequencies and percentages, and continuous data are summarized using descriptive statistics consisting of the number of subjects, mean, standard deviation, minimum, median, and maximum.

### 14.1.1 Efficacy analysis

#### 14.1.1.1 Primary endpoint

Regarding the rate of change in intact PTH level at the end of investigational product administration from pre-dose of investigational product on Day 1, the dose response profile will be investigated using seven contrast patterns for mean values in the KHK7580 0.5 mg group, 1 mg group, 2 mg group, and placebo group ([Table 14.1.1.1-1](#OLE_LINK1)). Resampling (permutation: number of extractions: 30,000, random seed: 7580005) will be used to adjust the multiplicity of the test. The significance level is a two-tailed p value of 5%. This is the principal analysis used for the study.

Table 14.1.1.1-1 Dose Response Profile (Contrast Pattern)

| Contrast pattern | Placebo group | KHK7580  0.5 mg group | KHK7580  1 mg group | KHK7580  2 mg group |
| --- | --- | --- | --- | --- |
| Monotonic decrease | 3 | 1 | -1 | -3 |
| Decrease from 1 mg | 3 | 3 | -1 | -5 |
| Decrease from 2 mg | 1 | 1 | 1 | -3 |
| Monotonic decrease (but 0.5 mg and 1 mg are roughly similar) | 1 | 0 | 0 | -1 |
| Monotonic decrease (but 1 mg and 2 mg are roughly similar) | 5 | 1 | -3 | -3 |
| Monotonic decrease (but 0.5 mg, 1 mg, and 2 mg are roughly similar) | 3 | -1 | -1 | -1 |
| Monotonic decrease (but placebo and 0.5 mg, and 1 mg and 2 mg are roughly similar) | 1 | 1 | -1 | -1 |

Regarding the rate of change in intact PTH level at the end of investigational product administration from pre-dose of investigational product on Day 1, the mean and 95% confidence interval for each group will be calculated by analysis of variance with treatment group as the factor. Descriptive statistics for each treatment group will be also shown. In addition, mean difference from the placebo group and 95% confidence interval will be calculated for the KHK7580 0.5 mg, 1 mg, and 2 mg groups and the KRN1493 25 mg group. Further, mean difference from the KRN1493 25 mg group and 95% confidence interval will be calculated for the KHK7580 0.5 mg, 1 mg, and 2 mg groups.

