## 4.5 Randomization and Blinding

### 4.5.1 Randomization

#### 4.5.1.1 Randomization method

Subjects who satisfy all the inclusion criteria will be randomly and evenly assigned to the KHK7580 0.5, 1, or 2 mg, or placebo group, or the KRN1493 25 mg group using a dynamic allocation method. The assignment factors are investigative site, history of treatment with cinacalcet hydrochloride, corrected serum Ca level at screening (< 9.0 mg/dL, ≥ 9.0 mg/dL), and intact PTH level at screening (< 500 pg/mL, ≥ 500 pg/mL). Details of the subject assignment procedure are described in the separately specified procedure.

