### 14.1.2 Analysis of Safety

All adverse events that occurred after the start of investigational product administration will be examined, and incidence rates will be summarized by treatment group according to the adverse event, whether or not a causal relationship could be ruled out, and the incidence rate by details. Incidence rate summarization by details will be performed by MedDRA/J SOC and PT. Summarization by severity will be also performed in a similar fashion. The mean and 95% confidence interval for each treatment group will be calculated for the following items by analysis of variance with treatment group as the factor. Descriptive statistics for each treatment group will be also shown.

• Lowest corrected serum Ca level from the start of investigational product administration until the end of follow-up

Descriptive statistics for laboratory values and vital sign measurements will be calculated for each item and each treatment group, and line graphs will be prepared. For ophthalmologic examination, a shift table before and after administration will be prepared. Descriptive statistics for electrocardiographic measurements will be calculated for each item and each treatment group, and line graphs will be prepared. For QTcF and QTcB, the number and percentage of subjects falling under each of the following categories will be shown for each treatment group.

• Test value after the start of administration (msec): <450, ≥450 and <480, ≥480 and <500, ≥500

• Change after the start of administration* (msec): <30, ≥30 and <60, ≥60

* Change = Test value at each assessment point - baseline test value

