## 25.12 Rationale for Establishing Target Number of Subjects

The following rates of change in intact PTH level are estimated at the end of administration in the placebo group and KHK7580 0.5 mg, 1 mg, and 2 mg groups with reference to outcomes in a Phase 1/2 clinical study of KHK7580 performed in Japan (7580-003 Study) and a Phase 2 clinical study of KRN1493 performed in Japan (KRN1493/03-A06 Study).

The results of the 7580-003 Study revealed that mean rate of change in intact PTH level at the end of repeated administration of 1 mg and 4 mg once a day for 14 days were −13.42% and −32.57%, respectively, and the standard deviations were 20.45% and 28.76%. In addition, the results from the KRN1493/03-A06 PPS revealed that mean rate of change in intact PTH level at the end of administration in the placebo group was 0.87% and the standard deviation was 22.47%.

On the basis of the above results, rate of change in intact PTH level at the end of administration in the present study is estimated as shown in [Table 25.12-1](#OLE_LINK2). The respective rates of change of −6.71% and −19.80% in the KHK7580 0.5 mg group and 2 mg group are linearly interpolated from the rate of change of 0% in the placebo group, the results at the end of repeated administration of 1 mg in the 7580-003 Study, and the results at the end of repeated administration of 1 mg and 4 mg in the 7580-003 Study. The standard deviation of 22.47% uses the standard deviation in the placebo group in the KRN1493/03-A06 Study.

Table 25.12-1 Estimated Rate of Change in Intact PTH Level at the End of Administration

| Group | Rate of change (%) | Standard deviation (%) |
| --- | --- | --- |
| Placebo group | 0 | 22.47 |
| KHK7580 0.5 mg group | −6.71 | 22.47 |
| KHK7580 1 mg group | −13.42 | 22.47 |
| KHK7580 2 mg group | −19.80 | 22.47 |

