On the basis of the above, a significance level with a two-tailed p value of 5% is used, multiplicity is taken into consideration by resampling (permutation: number of extractions: 30,000, random seed: 7580005, number of simulations: 10,000), and the probability of any of the contrast patterns set being significant is about 90% in a group of 28 subjects. In view of incidences of subjects excluded from the PPS, target subject numbers are set at five groups with 30 subjects in each and 150 subjects in total who are treated with the investigational product. In view of the number of subjects in the KRN1493 25 mg group (28 subjects) who exhibited a significant rate of change in intact PTH level in the KRN1493/03-A06 Study, target subject numbers in the KRN1493 25 mg group are set at 30 subjects in the same way as in other groups for the purpose of comparison and evaluation of efficacy and safety with the KHK7580 groups.

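### Allocation is balanced on cinacalcet history, Ca and PTH, but the principal test and ANOVA use treatment group only, so precision is forgone to the extent that these factors are prognostic

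*Protocol*

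**What the plan says.** Protocol 4.5.1.1 uses dynamic allocation to five equal groups: "The assignment factors are investigative site, history of treatment with cinacalcet hydrochloride", corrected serum Ca at screening (cut at 9.0 mg/dL) and intact PTH at screening (cut at 500 pg/mL).

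Section 14.1.1.1 defines the principal analysis as seven contrasts of the mean percent change in intact PTH across placebo and the three KHK7580 doses, tested at a two-sided 5% level. On multiplicity it says: "Resampling (permutation: number of extractions: 30,000, random seed: 7580005) will be used to adjust the multiplicity of the test". For estimation, "the mean and 95% confidence interval for each group will be calculated by analysis of variance with treatment group as the factor", followed by mean differences from placebo and from KRN1493 with 95% confidence intervals. Neither the test nor the ANOVA names an allocation factor or a baseline value, and no adjusted sensitivity analysis is given.

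Section 25.12 sizes the trial on an unadjusted SD of 22.47% and states that "the probability of any of the contrast patterns set being significant is about 90% in a group of 28 subjects".

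**The concern.** Balancing the groups on a prognostic factor removes most of that factor's contribution to chance differences between group means. A model with treatment as its only term does not know this and still counts the factor's variance as error. The stated standard errors of differences are then too large for this design. The test rejects less often than 5% under the null, the difference intervals cover more than 95%, and an adjusted analysis of the same data would be sharper.

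The sponsor's choice of these factors suggests that it thought imbalance in them would matter. Two entry criteria make some prognostic value plausible, though they do not show it: intact PTH has no upper limit (6.2), and cinacalcet users need only two weeks off drug before screening (6.3).

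Precision matters because the trial is meant to inform the starting dose (25.4). The planned steps between neighbouring groups are only 6.71, 6.71 and 6.38 points (25.12).

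**Working it through.** **Inputs from the protocol.** Two-sided 5% level and the seven contrasts (14.1.1.1); 28 evaluable subjects per group and SD 22.47% (25.12). Means are 0 for placebo, −13.42 for 1 mg, and for the other two doses "The respective rates of change of −6.71% and −19.80% in the KHK7580 0.5 mg group and 2 mg group are linearly interpolated". The 2 mg value checks: −13.42 + (−32.57 + 13.42)/3 = −19.80.

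**Not in the protocol.** R², the share of the variance of percent change that the allocation factors explain. It is varied from 0 upwards.

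**Step 1: reproduce the stated power.** For a contrast c, t = Σc·mean / (s·√(Σc²/n)). The linear contrast (3, 1, −1, −3) has Σcμ = −6.71 + 13.42 + 59.40 = 66.11 and expected t of about 66.11 / (22.47 × √(20/28)) = 3.48. The 95th percentile of the largest |t| over the seven contrasts with 4 × 27 = 108 df is 2.44 by simulation. The chance of exceeding it is 90.3%; a direct permutation simulation gives 90.1%. The stated figure of about 90% reproduces.

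**Step 2: ideal balance.** If the factors are fully balanced, the true variance of a contrast is (1 − R²)·σ²·Σc²/n, while the treatment-only analysis still estimates σ²·Σc²/n. Its standard error is too large by 1/√(1 − R²). An adjusted analysis works with residual SD 22.47·√(1 − R²), so the equivalent size without adjustment is 28/(1 − R²) per group.

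| R² | Type I error, unadjusted | Power, unadjusted | Power, adjusted | Excess width of difference CI | Equivalent n per group |
|---|---|---|---|---|---|
| 0 | 5.0% | 90% | 90% | 0% | 28 |
| 0.05 | 4.3% | 91% | 92% | 3% | 29.5 |
| 0.10 | 3.7% | 91% | 93% | 5% | 31 |
| 0.20 | 2.4% | 92% | 95% | 12% | 35 |

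**Step 3: imperfect balance.** The allocation algorithm is in a separate procedure, so minimisation was simulated: 4,000 trials of 140 subjects in five arms. Assumed were 25 sites, factor prevalences of 0.4, 0.6 and 0.3, and a biased-coin probability of 0.8. The adjusted model contains the three binary factors but not site. Half-widths are for 2 mg minus placebo, in percentage points.

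| R² | Type I error, unadjusted / adjusted | Power, unadjusted / adjusted | CI half-width, unadjusted / adjusted | CI coverage, unadjusted |
|---|---|---|---|---|
| 0 | 4.6% / 4.7% | 90.6% / 90.6% | 11.9 / 11.9 | 95.3% |
| 0.05 | 4.3% / 5.1% | 90.2% / 91.4% | 11.9 / 11.6 | 96.3% |
| 0.10 | 3.8% / 5.1% | 90.5% / 92.8% | 11.9 / 11.3 | 95.9% |
| 0.20 | 2.8% / 5.0% | 91.2% / 95.1% | 11.9 / 10.6 | 97.1% |

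The simulation error of a 5% rate is √(0.05 × 0.95 / 4,000) = 0.3 points, so the first row agrees with 5%. The unadjusted half-width agrees with 1.98 × 22.47 × √(2/28) = 11.9. The direction matches Step 2, and the conservatism at R² = 0.20 is slightly milder (2.8% against 2.4%).

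**The case against.** The strongest defence is that nothing planned is lost. The trial was sized on the unadjusted SD, an unadjusted test matches that calculation, and the promised power is delivered at every R² examined. For a phase 2 dose-response trial this is a defensible choice. That stands, and it limits the point to efficiency.

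The size is also unknown. Two of the factors are dichotomised screening values, and the outcome already divides by Day 1 PTH, so a small R² is as plausible as 0.20. At R² = 0 adjustment gains nothing. This stands, and it is why a range from 0 is shown. Exclusions from the per protocol set, which carries the principal analysis (14.7.2), can also disturb the balance.

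Section 14.6 leaves details to the analysis plan, which could restrict the permutation or add an adjusted analysis. A reader might infer from 14.1.1.1 that labels will be permuted freely across all subjects. The text gives only the number of extractions and the seed, so that is inference. The treatment-only ANOVA, however, is fixed in the protocol itself.

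A reader might extend the point to the lowest corrected Ca in 14.1.2, where means and intervals are also computed "for the following items by analysis of variance with treatment group as the factor". That section plans only per-group means and no difference between groups. The argument about over-wide difference intervals therefore does not apply there.

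**Conclusion.** The mismatch between allocation and analysis is real, and its direction is conservative. For an assumed R² of 0.05 to 0.20, an adjusted analysis would gain about 1 to 4 points of power and remove an excess of 3 to 12% in the width of difference intervals. That is worth roughly 1.5 to 7 extra subjects per group. At R² = 0 there is neither gain nor appreciable loss. The direction is firm; the size rests wholly on the assumed R² and on how well the allocation balances.

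A reader might infer that the trial is underpowered or that its type I error is wrong in the harmful direction. Neither follows: planned power of about 90% is met and actual type I error stays at or below 5%. Nor is Day 1 PTH one of the ignored balancing factors. The allocation uses screening PTH; Day 1 PTH is only a sensible baseline covariate. This is a worthwhile efficiency improvement and does not threaten the validity of the principal analysis.

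**What to change.** In 14.1.1.1, compute the seven contrasts and the mean differences from an ANCOVA with treatment, cinacalcet history, screening Ca stratum and baseline intact PTH (log Day 1 value or the screening stratum). For site, either include a random effect or state why it is left out. With about 30 subjects per group, a stated reason is enough.

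Name one permutation scheme that fits this model: permute residuals of the covariate model, or re-run the allocation algorithm. Permuting within history × Ca × PTH strata is less attractive, because 4 × 28 = 112 subjects over 8 strata and 4 arms leaves 112/32 = 3.5 per cell. Keep the unadjusted analysis as a sensitivity check, and make the change before unblinding.

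The cost is protocol and analysis-plan wording, slightly more code, and 3 to 4 of 108 degrees of freedom. All covariates are already collected. In the simulation at R² = 0, adjustment cost no visible power (90.6% either way).

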#### 14.1.1.2 Secondary Endpoints

The number and percentage of subjects who achieved the following and the exact 95% confidence interval for the percentage will be calculated for each treatment group.

• Achievement of a decrease in intact PTH level of ≥30% (rate of change from prior to investigational product administration on Day 1: ≤-30%) at the end of investigational product administration

• Achievement of an intact PTH level of ≤240 pg/mL at the end of investigational product administration

Descriptive statistics by timing of test and at the end of investigational product administration are shown for the following items by treatment group.

• Intact PTH level

• Whole PTH level

• Corrected serum Ca level

• Ionized Ca level

• Serum P level

• Intact FGF23 Level

• Corrected serum Ca-P product

### 14.1.2 Analysis of Safety

All adverse events that occurred after the start of investigational product administration will be examined, and incidence rates will be summarized by treatment group according to the adverse event, whether or not a causal relationship could be ruled out, and the incidence rate by details. Incidence rate summarization by details will be performed by MedDRA/J SOC and PT. Summarization by severity will be also performed in a similar fashion. The mean and 95% confidence interval for each treatment group will be calculated for the following items by analysis of variance with treatment group as the factor. Descriptive statistics for each treatment group will be also shown.

• Lowest corrected serum Ca level from the start of investigational product administration until the end of follow-up

Descriptive statistics for laboratory values and vital sign measurements will be calculated for each item and each treatment group, and line graphs will be prepared. For ophthalmologic examination, a shift table before and after administration will be prepared. Descriptive statistics for electrocardiographic measurements will be calculated for each item and each treatment group, and line graphs will be prepared. For QTcF and QTcB, the number and percentage of subjects falling under each of the following categories will be shown for each treatment group.

• Test value after the start of administration (msec): <450, ≥450 and <480, ≥480 and <500, ≥500

• Change after the start of administration* (msec): <30, ≥30 and <60, ≥60

* Change = Test value at each assessment point - baseline test value

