## 6.2 Inclusion Criteria

Subjects eligible for enrollment in the study had to meet all of the following criteria:

1) Personally submitted written voluntary informed consent to participate in the study

2) Aged ≥20 and <75 years old at the time of acquisition of consent

3) Stable chronic renal failure treated with hemodialysis 3 times weekly for at least 12 weeks before screening

4) Intact PTH level of ≥240 pg/mL at screening

5) Corrected serum Ca level of ≥8.4 mg/dL at screening

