#### 9.4.1.3 Blood biochemical tests-2

Parameters:

Corrected serum Ca^*1^, Ca, Alb, P, intact PTH, whole PTH, ionized calcium, intact FGF23

Timing of implementation:

• At screening^*1^ (prior to start of dialysis)

• Day 1 (prior to investigational product administration)

• Day 3, 5, 8, 15 (prior to investigational product administration and prior to start of dialysis)

• Day 22, 29 (prior to start of dialysis)

• Discontinuation

*1: If the serum Alb level is <4.0 g/dL, the serum Ca level will be corrected in accordance with the following formula. If the serum Alb level is ≥4.0 g/dL, the measured serum Ca level will be treated as the corrected serum Ca level.
Corrected serum Ca level (mg/dL) = Measured serum Ca level (mg/dL) +4-serum Alb value (g/dL)

*2: only for intact PTH, serum corrected calcium, Ca and Alb levels.

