## 25.9 Rationale for Establishing Test Items

The intact PTH level, whole PTH level, corrected serum Ca level, Ca level, Alb level, ionized Ca level, P, intact FGF23 level and the product of corrected serum Ca and P level are established to investigate the efficacy of KHK7580. The lowest corrected serum Ca level is established to investigate the safety of KHK7580.

Bone metabolism markers are established as the exploratory endpoints to investigate the impact on the bone, and carotid ultrasonography to investigate the effect on the parathyroid volume and blood flow.

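### Lowest corrected serum Ca is summarised only as a raw level by group; a baseline-adjusted analysis with between-group differences could be added at no cost

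*Protocol*

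**What the plan says.** Section 14.1.2 defines the variable as "Lowest corrected serum Ca level from the start of investigational product administration until the end of follow-up". The planned output is a mean with a 95% interval per group, produced "for the following items by analysis of variance with treatment group as the factor", plus descriptive statistics. No baseline term, allocation factor or between-group difference is named for this item. No other safety item receives a confidence interval.

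For the primary endpoint, section 14.1.1.1 does name differences: "mean difference from the placebo group and 95% confidence interval will be calculated for the KHK7580 0.5 mg, 1 mg, and 2 mg groups". It also names the difference from placebo for KRN1493, and the differences of the three KHK7580 groups from KRN1493.

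Other sections bear on the choice:
- Section 9.4.1.3 schedules corrected serum Ca before the first dose on Day 1, with no restriction by group.
- Section 4.5.1.1 makes screening corrected Ca, split at 9.0 mg/dL, one of the four allocation factors.
- Section 6.2 sets an entry floor: "Corrected serum Ca level of ≥8.4 mg/dL at screening".
- Section 25.9 gives the purpose of the endpoint: "The lowest corrected serum Ca level is established to investigate the safety of KHK7580".
- Sections 25.1 and 25.12 say that the KRN1493 arm serves comparison of safety as well as efficacy.

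**The concern.** A subject's lowest Ca plausibly depends on where that subject started. If so, a model with treatment group alone leaves the between-subject spread in starting Ca in the error term, and any chance difference in Day 1 Ca between arms carries straight into the comparison of their means. Allocation on a two-level screening value limits such differences but cannot remove them.

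The protocol also says that safety is to be compared between arms, yet gives only separate group means for the one safety measure it chose to estimate with intervals. A reader who wants the effect of a dose on lowest Ca against placebo or KRN1493 would have to work it out from those means, without adjustment.

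The measure matters for dose choice. Section 1.4.3 reports decreased blood calcium in 8 of 24 patients on multiple doses of 4 mg in Study 7580-003, three of whom discontinued. Section 25.4 says that the trial is to inform the starting dose. The 4 mg dose is twice the highest KHK7580 dose studied here, so that rate does not transfer directly.

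**Working it through.** **The plan's own figures.** The protocol states no SD, interval width or power for lowest Ca, so there is no such figure to reproduce. Its only power statement, about 90% with 28 per group for the primary endpoint (section 25.12), reproduces: a simulation of the largest contrast statistic over the seven patterns gives 90.3%. It does not depend on the Ca analysis.

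**Inputs.** There are 30 subjects in each of 5 groups, so N = 150 (section 25.12). Let SD be the within-group standard deviation of lowest Ca, and r the within-group correlation between Day 1 and lowest Ca. The documents give neither. Results are therefore in SD units, and r is varied as an assumption.

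**Unadjusted half-widths of the 95% interval (N − 5 = 145 df).**
- Group mean, as planned: t × SD / √30 = 0.361 SD.
- Difference between two groups, not planned: t × SD × √(2/30) = 0.510 SD.

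**Adjusted half-width for a difference (N − 6 = 144 df).** The formula is t × SD × √(1 − r²) × √(2/30) × √(1 + 1/143). The last factor is the average cost of estimating the slope.

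| r (assumed) | Adjusted half-width | Unadjusted wider by |
|---|---|---|
| 0 | 0.512 SD | about 0% (adjusted is 0.4% wider) |
| 0.3 | 0.489 SD | about 4% |
| 0.5 | 0.444 SD | about 15% |
| 0.7 | 0.366 SD | about 40% |
| 0.8 | 0.307 SD | about 66% |

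For illustration, with an assumed SD of 0.6 mg/dL the unadjusted half-width for a difference is 0.510 × 0.6 = 0.306 mg/dL. Adjusted, it is 0.444 × 0.6 = 0.266 at r = 0.5 and 0.366 × 0.6 = 0.220 at r = 0.7.

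**Chance imbalance.** Under simple randomisation, the standard error of the difference in mean Day 1 Ca between two arms is √(2/30) = 0.258 baseline SDs. The regression slope is r times the ratio of the two SDs. An imbalance of one standard error therefore shifts the unadjusted difference by 0.258 × r SD of lowest Ca: 0.129 SD at r = 0.5 and 0.181 SD at r = 0.7. Allocation on screening Ca should make typical imbalances smaller than this.

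**Why a covariate and not a change score.** With equal variances, the SD of a change relative to the raw level is √(2(1 − r)): 1.18 at r = 0.3, 1.00 at 0.5 and 0.77 at 0.7. A change score is less precise than the raw level when r is below 0.5. The covariate model loses almost nothing at any r.

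**The case against.** The strongest reply is that nothing planned here is faulty. Section 14.1.2 asks for a mean and interval per group, which is an ordinary valid summary of the lowest Ca on each dose. Where differences are wanted, the protocol names them, as it does for PTH. The raw level also has clear meaning, because the protocol's own Ca limits are absolute: 7.5 mg/dL or below for discontinuation (section 12.1.1) and recovery to at least 8.4 mg/dL as the guide for adverse event follow-up (section 9.7.2). All of this stands, and it is why the raw summary should stay.

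Stronger readings that a reader might infer are not supported:
- *That the plan compares arms with intervals much wider than necessary.* No difference is planned, and the excess width depends on a correlation that the documents do not give. The entry floor of 8.4 mg/dL restricts the baseline range, which tends to lower it.
- *That the planned intervals are too wide because allocation was balanced on Ca.* That argument concerns differences between arms, not the per-group intervals in the plan.
- *That the raw level is the least precise option available.* A change score is worse when r is below 0.5.
- *That lowest Ca is the key safety endpoint.* It is one of six unranked safety endpoints in section 4.3.2.
- *That the minimum should come from scheduled visits only.* The protocol shows no error on this, and the restriction would drop observed low values from a safety table.

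What survives the reply is narrower: comparing safety between arms is a stated purpose, a baseline value is already collected, and the plan does not use it for this endpoint.

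**Conclusion.** The point holds as a free improvement, not as an error. The treatment-only analysis of the raw lowest Ca is valid for what it reports, but it provides no between-group estimate and ignores a baseline value that is collected anyway. The gain from adjustment rests on the assumed correlation: a difference interval without adjustment would be about 0% wider at r = 0, 4% at 0.3, 15% at 0.5 and 40% at 0.7. Only near the top of that range is the gain large, and the documents cannot say where the true value lies. The cost of adjusting is negligible even when baseline Ca is uninformative (0.512 against 0.510 SD), and adjustment also allows for chance Day 1 imbalance. No figure in the protocol is wrong, and the primary analysis and sample size are untouched.

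**What to change.** In section 14.1.2, keep the planned raw means, 95% confidence intervals and descriptive statistics by group, with all observed minima. Add one sentence: lowest corrected serum Ca will also be analysed by analysis of covariance with treatment group and Day 1 pre-dose corrected Ca as a continuous covariate. This analysis will report adjusted group means, differences of each KHK7580 group and of KRN1493 from placebo, and differences of each KHK7580 group from KRN1493, all with 95% confidence intervals. The set of differences then matches the one already planned for PTH in section 14.1.1.1.

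The cost is that sentence and one extra table. No new data, visits or subjects are needed, and section 14.6 allows the analysis details to be settled before the data are finalised.
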